Overall, only a limited number of studies have been conducted that investigated the effectiveness of different types of treatments for stretch marks, specifically comparing two different types of treatment. Taking that into account and considering the characteristics of both fractional CO_2_ laser and fractional radiofrequency, we would like to focus this work on the evaluation and comparison of the clinical efficacy and treatment safety of both techniques in clinical applications (STRIAL). To evaluate the impact of stretch marks reduction on the quality of life and on body image, two hypotheses are proposed: the clinical efficacy and safety of fractional CO_2_ laser are superior to fractional radiofrequency, or the clinical efficacy and safety of fractional radiofrequency are superior to the fractional CO_2_ laser.

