## 2. Materials and Methods

### 2.1. Study Design

We propose a randomized controlled trial, 1 to 1, that aims to compare the clinic efficacy and safety of two different treatments for striae: fractional CO_2_ laser treatment versus fractional radiofrequency (FRF). This trial will be conducted according to the trial procedure presented in the flowchart in Figure 1.

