### 2.5. Intervention

Regarding the clinical procedures, the CO_2_ laser (CO_2_RE^®^, Candela, Marlborough, MA, USA) group will undergo three sessions, once a month over 3 months. The laser procedure has the following indications: laser tip diameter from 1 to 10 millimeters (mm), according to the width of the lesions; pulse power of 100 W; and repetition rate of 20 Hz using a single pass. During this procedure, a cryotherapy advice (Cryo 6, Zimmer, Germany) will be applied to reduce any pain. Since laser absorption is related to skin properties [28], there is a need to have both the reflectance and absorbance spectra of human skin. This is the key to quantitatively and non-invasively analyzing skin components. Figure 2 represents the relative penetration of different wavelength in all skin layers. Figure 3 represents a hyperspectral skin image, with the reflectance of different wavelength in the visible light range.

The FRF group will also undergo three sessions, once a month over 3 months. The procedure of this treatment will be performed with a set of 24 RF conductive needles. Each needle has a length of 2500 micrometers (μm). Patients will receive initial doses of 20–40 mJ/pin, and the doses will be increased at each session based on patient tolerance. All treated areas will receive a pass based on the treatment site and patient tolerance. During this procedure, cryotherapy will be applied with a Zimmer G system to reduce the patient’s pain.

For clinical improvement, before and after photos of an individual that went through laser CO_2_ treatment for abdominal striae will be used as a control (Figure 4); high-resolution digital photographs will be taken before and after both treatments at every session, starting at the baseline. Two physicians blinded to the study will compare these photographs using quartile scoring criteria for the assessment (0 = no improvement; 1 = mild (25% improvement); 2 = moderate (>25 ≤ 50% improvement); 3 = good (>50 ≤ 75% improvement); 4 = excellent (≥76% improvement)).

Additionally, measurements of cutaneous temperature, pH, and skin elasticity will be taken at the baseline and before and after each treatment. Cutaneous temperature will be measured by a thermograph (FLIR i7), positioned at 7 cm away from the abdomen area. The skin pH will be measured by pH bands. The skin elasticity will be measured by an elastometer.

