## 3. Results

### 3.1. Primary Outcome

The primary outcome measure will focus on the change in the quartile scoring criteria by comparing the digital photos taken before and after each treatment (fractional CO_2_ laser and FRF) for clinical improvements in the affected area (abdomen). This process will be assessed by two physicians blinded to the study. Figure 4 will be the control, being compared to the pictures taken during the study.

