## 4. Discussion

As we mentioned before, from a previous review of the literature, we concluded that for an accurate assessment of efficient treatments for striae, more clinical studies with a significant sample are necessary. Therefore, our trial seems to be an innovative study exploring the influence of stria treatment on the health-related quality of life of patients undergoing fractional CO_2_ laser or fractional radiofrequency treatment. To overcome some limitations found in the literature, we propose a randomized controlled trial with a sample of 60 individuals. This sample would be important to increase the probability of including both men and women and participants with different types of skin and strial bands.

With the proposed trial, we expect to validate the fractional CO_2_ laser and fractional radiofrequency protocols in terms of efficacy and safety, which can be useful in the management of physical characteristics linked to striae. With this study design, we expect to find evidence that the treatments could demonstrate significant differences, such as a reduction in the length and width of striae bands. With respect to the primary outcomes, we will explore the quartile scoring criteria prepared for the assessment of clinical improvements in the affected area (abdomen) before and after the respective treatments, and we expect to see differences by comparing the digital photos taken in these timelines, using Figure 4 as the control. Regarding the secondary outcomes, we will explore the measurements of cutaneous temperature, skin pH, and skin elasticity to assess any inflammatory processes and to describe differences in different skin aspects after each treatment.

In addition, we will try to assess the impact of stretch mark reduction on body image, through a scale that evaluates the quality of life, the BODY-Q^TM^ Scale—Appraisal of Stretchmarks. 

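### The stated primary comparison is before versus after under each treatment, with an external photograph as control, while the hypotheses compare CO2 laser with FRF

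*Protocol article*

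**What the plan says.** **The question asked.** Section 1 (Introduction) gives two hypotheses. One is that "the clinical efficacy and safety of fractional CO_2_ laser are superior to fractional radiofrequency"; the other is the reverse. Section 2.1 describes a 1:1 randomised trial that "aims to compare the clinic efficacy and safety of two different treatments for striae". Section 5 (Conclusions) also speaks of comparing the two treatments.

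**The primary outcome.** Section 3.1 gives it as the "change in the quartile scoring criteria by comparing the digital photos taken before and after each treatment (fractional CO_2_ laser and FRF", and adds that "Figure 4 will be the control, being compared to the pictures taken during the study". Figure 4 shows one individual treated with CO2 laser. The Discussion restates the primary outcome in terms of improvement "before and after the respective treatments, and we expect to see differences by comparing the digital photos taken in these timelines", again with Figure 4 as control. It also says that "we expect to validate the fractional CO_2_ laser and fractional radiofrequency protocols in terms of efficacy and safety".

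**The score and the photographs.** Section 2.5 rates improvement from 0 to 4, beginning "0 = no improvement; 1 = mild (25% improvement". There is no category below 0. The same section says that "high-resolution digital photographs will be taken before and after both treatments at every session, starting at the baseline".

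**The significance rule.** Section 3.5 sets p < 0.05 and does not attach it to a particular comparison.

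**The concern.** The comparison stated for the primary outcome is not the comparison in the hypotheses. Section 3.1 contrasts time points and joins the two treatments with *and*. Section 3.2, on the secondary outcomes, sets one treatment against the other with *versus*. The only thing section 3.1 calls a control is a pair of photographs from one person outside the randomised groups, treated with one of the two study treatments.

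Two things are at stake.

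- **The hypotheses.** A before/after result in each group, or a comparison with Figure 4, does not show which treatment is better. Only the randomised difference between groups does.
- **Per-arm efficacy claims.** The score is already a judgement of improvement and cannot register worsening. Rating error in an untouched abdomen can only move it up from 0, so errors do not cancel. With no untreated arm, a mean above 0 cannot be separated from lenient rating, photographic variation or natural change. Wording about validating both protocols encourages this kind of claim.

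**Working it through.** **1. The statements side by side**

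| Place in the Protocol article | Comparison described |
|---|---|
| Abstract; 1 (hypotheses); 2.1 (aim); 5 | CO2 laser against FRF |
| 3.1 (primary outcome) | Before against after, under each treatment; also study photographs against Figure 4 |
| 3.2 (secondary outcomes) | CO2 laser against FRF |
| 4 (primary outcome restated) | Before against after, with Figure 4 as control |
| 4 (expected result) | Both protocols validated |
| 3.5 | p < 0.05, comparison not specified |

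The between-arm question is clear from the first row. The mismatch is confined to the primary outcome and its restatement in the Discussion.

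**2. Inputs for an illustration**

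- From the documents: 30 per group (section 2.2), score 0 to 4 with 0 as the floor (section 2.5), threshold 0.05 (section 3.5).
- Assumed: a two-sided test; a within-arm test of the score against 0, which the document does not name; and a probability q that a participant whose striae have not truly changed is still rated 1 or more. The documents give no value for q, so a range is shown.

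**3. Scores needed for within-arm significance**

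Every non-zero score is positive, so with k non-zero scores the exact two-sided sign test gives p = 2 × 0.5^k.

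- k = 5: 2 × 0.5^5 = 0.0625
- k = 6: 2 × 0.5^6 = 0.031

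Six of 30 participants (20%) rated 1 or more would be enough, with the other 24 at 0.

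A one-sample t-test needs fewer. With four scores of 1 and 26 of 0:

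- mean = 4/30 = 0.133
- SD = √[(30/29) × 0.133 × 0.867] = 0.346
- SE = 0.346/√30 = 0.063
- t = 2.11 on 29 df, p = 0.043

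With three scores of 1, p = 0.083.

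**4. Chance that an ineffective arm is called effective**

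K follows a Binomial(30, q) distribution. The sign test rejects when K ≥ 6. The t-test, with spurious scores taken as 1, rejects when K ≥ 4.

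| q (assumed) | Sign test, P(K ≥ 6) | t-test, P(K ≥ 4) |
|---|---|---|
| 10% | 0.07 | 0.35 |
| 15% | 0.29 | 0.68 |
| 20% | 0.57 | 0.88 |
| 30% | 0.92 | 0.99 |

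At q = 20% in both arms, the chance that exactly one arm is significant by the sign test is 2 × 0.572 × (1 − 0.572) = 0.49. Reading that as superiority of one treatment would be wrong, because the arms are identical.

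**5. The between-arm contrast under the same conditions**

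In 4,000 simulated trials per scenario, with 30 per arm and identical score distributions in the two arms, t and Mann-Whitney tests between arms rejected in about 4% to 6% of trials. That is the nominal rate. Leniency common to both arms does not produce a false difference.

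**The case against.** The strongest reply is that section 3.1 defines a variable, not a contrast. Many two-arm trials score each participant's change and then compare groups, and the parenthesis naming both treatments may mean only that photographs are scored in both. The Abstract sets CO2 laser against FRF and then says results are assessed by the quartile score. Sections 1, 2.1 and 5 point the same way, and no hypothesis concerns a single arm. Section 3.5 names no test, and an article may leave the choice of test to a fuller document.

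Much of this stands. A reader might infer that the trial plans a within-arm test, that its primary result is therefore nearly bound to be significant, or that the document gives no guide to which comparison matters. The documents support none of these. No test against 0 appears, the document as a whole favours the between-arm reading, and at q = 10% the sign test would reject in only 0.07 of trials. The probabilities above describe a hypothetical analysis with an assumed q, and they reduce two blinded physicians' ratings to a single spurious-or-not score. The missing name of a test is not part of this point.

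The reply does not remove the mismatch. The article does state a comparison for the primary outcome: before against after, with Figure 4 as control. The Discussion repeats it and adds an expectation about each protocol separately. This is text that disagrees with the hypotheses, not detail left for later, and a later analysis plan could follow either reading and claim to agree with the article.

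**Conclusion.** The point holds as an inconsistency between the stated primary comparison and the stated hypotheses. It does not show an invalid test in the plan. Followed literally, section 3.1 and the Discussion would not answer whether CO2 laser or FRF is better, and would invite efficacy claims for each arm that neither the score nor the design can support.

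The size of the risk depends on a within-arm test being run and on q. Under the sign test, a false claim for one arm ranges from 0.07 (q = 10%) to 0.92 (q = 30%). It is close to automatic only from about 30% upwards. If the quartile score is compared between the randomised groups, as the aim implies, the endpoint is legitimate and this risk does not arise.

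**What to change.** - **Section 3.1:** state that the primary contrast is Group A versus Group B on the blinded quartile score, comparing baseline with one named post-treatment assessment.
- **Section 3.1, per-arm results:** report each group's score distribution descriptively, without within-arm p-values.
- **Figure 4 (sections 2.5, 3.1 and 4, and the figure caption):** stop calling it the control, or relabel it as a reference image only.
- **Discussion:** recast the primary-outcome sentence, and the wording about validating both protocols, as the comparison between the two groups.

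The trial gives up per-arm efficacy claims. The changes are to wording only and need no new data or patients.

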**Figure 4 healthcare-10-02372-f004:**
[figure not shown]
Before (**A**) and after (**B**) control photos of abdominal striae of an individual subjected to laser CO_2_ treatment.

**Table 1 healthcare-10-02372-t001:** Timing of visits and data collection, according to the Standard Protocol Items: Recommendations for Interventional Trials (SPIRIT).

				Treatment Period		
		Screening	Baseline 0-Month	1-Month	2-Month	3-Month
Patient	Eligibility Informed consent Clinical data Physical examination Randomization	X	X X X X			
Intervention	Fractional CO_2_ laser: Group A			1 session per month for 3 months		
	Fractional radiofrequency: Group B			1 session per month for 3 months		
Outcomes	Digital photo collection		X	X	X	X
	Cutaneous temperature		X	X	X	X
	Skin pH		X	X	X	X
	Skin elasticity		X	X	X	X
Participant Safety	Adverse effects			X	X	X

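### The primary outcome names photographs of one CO2-laser-treated individual (Figure 4) as the control, which conflicts with the before/after score and with the randomised comparator

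*Protocol article*

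**What the plan says.** The protocol article gives Figure 4 the role of control in four places.

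- Section 2.5 (Intervention): "before and after photos of an individual that went through laser CO_2_ treatment for abdominal striae will be used as a control".
- Section 3.1 (Primary Outcome): "Figure 4 will be the control, being compared to the pictures taken during the study". Nothing limits this to one arm.
- Section 4 (Discussion), on the primary outcome: "we expect to see differences by comparing the digital photos taken in these timelines, using Figure 4 as the control".
- The caption of Figure 4: "control photos of abdominal striae of an individual subjected to laser CO_2_ treatment".

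The article also describes the outcome and the design in other terms. Section 3.1 defines the primary outcome as the "change in the quartile scoring criteria by comparing the digital photos taken before and after each treatment". Section 2.5 has photographs taken at every session from baseline, and then: "Two physicians blinded to the study will compare these photographs using quartile scoring criteria for the assessment". The scale runs from 0 to 4, and each grade above 0 is a band of percent improvement. Sections 2.1, 2.2 and 2.4 describe a 1:1 randomised comparison of CO2 laser (Group A, n = 30) with fractional radiofrequency (Group B, n = 30).

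**The concern.** The primary outcome has two reference points, and the article does not say which one governs the score. One is the earlier photograph in a before/after pair. The other is another person's abdomen. A rater who follows Section 3.1 literally would hold each trial photograph against Figure 4. The resulting grade would then mix improvement with differences in starting severity, skin, stria type and photography between that person and the participant.

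The reference is also not neutral. Figure 4 shows a response to CO2 laser, which is the Group A treatment, yet it would be the yardstick for radiofrequency participants as well. The scoring of the trial's main endpoint is at stake, and so is the meaning of any later report that results were better or worse than the control.

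**Working it through.** The article gives no effect size, standard deviation or power for this outcome, so there is no figure to reproduce. The check sets the statements side by side.

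**1. Is it a slip?** No. Section 2.5, Section 3.1, the Discussion and the caption all use the same word for the same image. Section 3.1 goes further and says what is done with it: it is compared with the study pictures.

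**2. Who is in Figure 4?** The text says only that it is an individual who had CO2 laser. The photographs already appear in an article that describes the trial in the future tense, so this person was not randomised in it. That is an inference, but a safe one.

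**3. Does the control fit the score?** No. A grade of percent improvement needs a before and an after for the same skin. No grade on the 0 to 4 scale refers to Figure 4, so the scale cannot be applied to a comparison of a participant with a different person.

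**4. Does the control fit the design?** No. In a two-arm trial randomised 1:1, the comparator is the concurrent other arm, here 30 against 30. Figure 4 adds a third reference: n = 1, not randomised and not concurrent. One person gives no estimate of between-person variability, so no valid standard error or test against that control exists.

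**5. What could it do to the comparison of the arms?** Suppose that showing Figure 4 shifts the average grade by a in Group A and by b in Group B. Then:

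observed difference = difference without the image + (a − b)

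If a = b, the shift cancels (setting aside the floor and ceiling of the scale). If resemblance to a CO2-type result affects grading, a and b can differ and the difference between arms is biased by a − b. The article gives nothing from which to estimate a or b, so neither the size nor the direction can be stated.

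**The case against.** The best defence is that Figure 4 was meant only as a visual guide. Sections 2.5 and 3.1 already tie the score to before and after photographs, and no grade mentions Figure 4. The article consistently describes a randomised comparison of the two treatments, and the Conclusions look to differences between them. A fixed image shown alike for both arms is common to both, and randomisation balances participants' severity and skin type in expectation. The raters are also described as blinded.

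Much of this stands. A reader might infer that the protection of randomisation is lost. The documents do not support that: Section 3.5 names no test against Figure 4, and the 30 against 30 contrast can still be made. A reader might also set the precision of a single control against that of a 30-person arm. That would assume Figure 4 is graded and entered as a comparator in an analysis, which no section describes. Nor do the documents show that the difference between arms is biased.

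The defence does not remove the stated rule. The article nowhere calls Figure 4 an illustration or a guide; it calls it the control and says that study pictures are compared with it. Even as a guide, it would show the raters one arm's modality only. Blinding does not cure this, because the anchor lies in the reference image and not in knowledge of the allocation.

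**Conclusion.** Wrong as written. This is a positive statement about the primary outcome, so it is not a detail that a fuller protocol or analysis plan could simply supply. Followed literally, it would judge all 60 participants against one non-randomised result from the Group A modality, and it contradicts both the article's scale and its design.

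The firm part is the contradiction, together with the fact that one person cannot support an inference against a control. Anchoring that differs between arms is a plausible risk of unknown size; it would need raters to see Figure 4 while scoring and to respond to it differently for the two treatments. The randomised contrast of CO2 laser with radiofrequency remains available. The conclusion rests on two readings: that control and compared mean what they say, and that the individual in Figure 4 is not a trial participant.

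**What to change.** - In Sections 2.5, 3.1 and 4 and in the Figure 4 caption, remove the word control.
- In Sections 2.5 and 3.1, state that each participant's own baseline photograph is the reference for the quartile score, and that the other randomised arm is the comparator.
- Label Figure 4 as illustration only, and state that it is not shown to the two physicians during scoring.

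The cost is wording in four places. No participants, visits, measurements or treatment procedures change. It should be done before any photograph is graded, because grades already given against Figure 4 would have to be repeated.

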### 3.2. Secondary Outcome

Secondary outcome measures will focus on data changes regarding cutaneous temperature and skin pH and elasticity, assessed after the stria treatments (fractional CO_2_ laser versus FRF). Cutaneous temperature will be measured by a thermograph (FLIR E1), which will help to evaluate any inflammatory process; skin pH will be measured by pH bands; and skin elasticity will be measured by an elastometer.

### 3.3. Participant Timeline

The timeline of the study visits, enrolment process, interventions, and assessments carried out on the participants will be reported according to the Standard Protocol Items: Recommendations for Interventional Trials (SPRIT) guidelines [31], as shown in Table 1.

### 3.4. Adverse Events

Adverse events will be monitored for each treatment during the trial. Any adverse events or reactions that are thought to be causally associated with the intervention, such as discomfort, mild pain, tissue erythema, tissue edema, irritation, and hyperpigmentation or hypopigmentation of the tissue, will be reported and managed. The measurement of cutaneous temperature before and after the treatments will help us monitor any sudden and significant changes regarding inflammatory processes. If the individual performs any additional physical therapy a day before or 3 days after the treatment, it will also increase the possibility of erythema and irritation since heat is being applied to the skin, so it is not advisable to perform exercise during this time.

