### 3.5. Data Collection and Statistical Analysis

Data collection will be performed in every session for each treatment. The data from this study will be analyzed using the Statistical Package for the Social Sciences (SPSS) V.21 software. A *p*-value < 0.05 will be considered statistically significant. Measured data will be expressed as mean ± SD.

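### The same-session change in skin temperature is read as inflammation, although cryotherapy and device heat come between the two readings in both arms

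*Protocol article*

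**What the plan says.** Protocol article, section 2.5 (Intervention), sets the timing: "measurements of cutaneous temperature, pH, and skin elasticity will be taken at the baseline and before and after each treatment". Section 3.5 places collection at the treatment visit: "Data collection will be performed in every session for each treatment".

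Section 2.5 also cools the skin during the procedure in each arm. For the CO2 laser, "a cryotherapy advice (Cryo 6, Zimmer, Germany) will be applied to reduce any pain"; for fractional radiofrequency (FRF), "cryotherapy will be applied with a Zimmer G system".

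Two sections then give the temperature reading a meaning. Section 3.4 (Adverse Events) states: "The measurement of cutaneous temperature before and after the treatments will help us monitor any sudden and significant changes regarding inflammatory processes". Section 3.2 (Secondary Outcome) lists cutaneous temperature as an outcome, measured with a thermograph, "which will help to evaluate any inflammatory process". The Discussion repeats the link between the secondary measurements and inflammation.

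Table 1 shows temperature at months 0, 1, 2 and 3 only.

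**The concern.** A before-to-after contrast can be attributed to inflammation only if nothing else that moves skin temperature acts between the two readings. Here two other things do, by design: cold is applied for pain relief, and the device puts heat into the tissue. The article therefore fixes a measurement and an interpretation that do not fit together.

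Two uses are at stake. As a safety signal, the reading could stay flat or fall in a participant whose skin is inflamed, or rise in one whose skin is merely still warm from the device. As a secondary outcome, a difference between arms could show how the two procedures heat and cool the skin rather than how much inflammation each provokes. Randomisation does not help with the second problem. It balances participants, whereas cooling and heating are part of each arm's procedure. A larger sample would not remove the bias either.

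**Working it through.** The article gives no temperature effect, standard deviation, threshold or sample-size calculation, so there is no figure to reproduce. The check sets the statements side by side.

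**1. What lies between the readings**
- Cooling, both arms: cryotherapy during the procedure (section 2.5).
- Heat, CO2 laser: the Introduction describes small zones of thermal damage.
- Heat, FRF: the Introduction describes heating of the dermis.
- Section 3.4 itself acknowledges that treatment applies heat to the skin.

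**2. What the contrast contains**

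For one session,

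after − before = −C(t) + H(t) + I(t),

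where t is the time from the end of cooling to the second reading, C is residual cooling, H is residual device heat and I is inflammatory warming. Only I is wanted. The article gives no value for t, C, H or I. If C exceeds H + I, the reading falls even though I is positive (masking). If H exceeds C and I is zero, the reading rises without inflammation (mimicking). Neither the sign nor the size of the change identifies I.

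**3. Between arms**

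The difference in mean change is −ΔC + ΔH + ΔI. The heat source differs by arm, so ΔH cannot be taken as zero. Section 2.5 also raises the FRF energy from session to session according to tolerance, so H need not be constant within that arm. Whether ΔC differs from zero is not established.

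**4. Why the delay matters (illustration on assumed values)**

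The following inputs are assumptions and do not come from the article: cooling lowers the surface by 5–15 °C, skin re-warms exponentially with a time constant τ of 3–10 min, and inflammation adds 0.5–2 °C. Residual cooling is drop × exp(−t/τ).

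| t | Smallest (5 °C, τ = 3) | Largest (15 °C, τ = 10) |
|---|---|---|
| 0 min | 5 °C | 15 °C |
| 5 min | 5 × exp(−5/3) = 0.9 °C | 15 × exp(−0.5) = 9.1 °C |
| 10 min | 5 × exp(−10/3) = 0.2 °C | 15 × exp(−1) = 5.5 °C |
| 30 min | 5 × exp(−10) ≈ 0 °C | 15 × exp(−3) = 0.75 °C |

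This covers C alone and leaves out H, which acts in the opposite direction, so it says nothing about the net sign. It shows only that residual cooling can exceed the assumed signal at short delays and is small at long ones. The timing of the second reading therefore decides whether it can be interpreted.

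**5. Which readings are clean**

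Readings taken before sessions 2 and 3 come about a month after the previous session and carry no same-day cooling or device heat. They can show persistent inflammation. They cannot show the sudden changes that section 3.4 is after. If the three sessions fall at months 1, 2 and 3, no pre-session reading follows the last one.

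**The case against.** The strongest reply is that this is a condensed article. The delay before the second reading is a procedural detail that a full protocol may well give, and a long enough delay would largely remove the problem; at 30 min the illustration leaves at most 0.75 °C of cooling. This stands in part, and it is why the point is conditional on the delay. It does not dispose of the point, because the article itself states both the measurement across a cooled and heated session and its reading as inflammation, and those stated choices conflict unless a delay is added.

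Three stronger readings are tempting, and the documents do not support them:

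- *That cooling dominates, so the monitor fails by missing inflammation.* Device heat pushes the other way and no magnitudes are given. False alarms are as possible as missed signals.
- *That the arms are cooled differently.* The article names "Cryo 6, Zimmer, Germany) will be applied to reduce any pain" for one arm and "During this procedure, cryotherapy will be applied with a Zimmer G system" for the other. Both are Zimmer systems, and the naming is loose elsewhere (the thermograph is FLIR i7 in section 2.5 and FLIR E1 in section 3.2). One device named in two ways is plausible, and nothing shows different strength or duration.
- *That participant safety rests on this reading.* Section 3.4 says only that it helps monitoring. No threshold or decision is tied to it, and erythema, edema, irritation, pain and pigment change are followed separately.

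It is also fair to say that section 3.2 does not restrict the secondary outcome to the same-session contrast, and that the cleaner pre-session data are already collected. This makes the remedy cheap; it does not settle which contrast will be used.

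**Conclusion.** The point holds in conditional form. As the article is written, cryotherapy and device heating separate the two readings in both arms, so the same-session temperature change mixes cooling, device heat and inflammation. It can mask or mimic inflammation unless the second reading is delayed long enough, and no such delay is stated. A between-arm difference may reflect the procedures, because the heat source differs.

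The size and net direction cannot be derived from the document; the illustrative figures rest wholly on assumed inputs and omit device heat. The consequence is limited to one secondary outcome and one auxiliary safety signal. The primary outcome, the photographic quartile score, is unaffected. The matter deserves correction before the data are collected, but it does not threaten the trial's main comparison.

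**What to change.** 1. Define the secondary temperature outcome as the change from baseline to the readings taken before later sessions (sessions 2 and 3). These are already scheduled, so this needs wording only. State that, depending on how the sessions map to Table 1, no such reading may follow the last session, in which case the outcome covers only the effects of sessions 1 and 2.
2. Take the acute reading at one fixed interval after cooling ends, identical in both arms, and record the actual time. The sponsor should choose and justify the interval; the documents give no basis for a specific value. If this is not feasible, keep the reading as a description and do not interpret the same-session change as inflammation.
3. Optionally, also read adjacent untreated abdominal skin. This corrects for room and body temperature only. It does not remove local cooling or device heat, so it cannot replace the fixed interval.

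The cost is a few lines of protocol text and a slightly longer visit, plus one extra non-contact reading if item 3 is adopted. Treatment and cooling remain as they are.
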